## Abstract

**Background:**

Balance dysfunction and falls are common problems in later stages of dementia. Exercise is a well-established intervention to reduce falls in cognitively intact older people, although there is limited randomised trial evidence of outcomes in people with dementia. The primary objective of this study is to evaluate whether a home-based balance exercise programme improves balance performance in people with mild to moderate severity Alzheimer's disease.

**Methods/design:**

Two hundred and fourteen community dwelling participants with mild to moderate severity Alzheimer's disease will be recruited for the randomised controlled trial. A series of laboratory and clinical measures will be used to evaluate balance and mobility performance at baseline. Participants will then be randomized to receive either a balance training home exercise programme (intervention group) from a physiotherapist, or an education, information and support programme from an occupational therapist (control group). Both groups will have six home visits in the six months following baseline assessment, as well as phone support. All participants will be re-assessed at the completion of the programme (after six months), and again in a further six months to evaluate sustainability of outcomes. The primary outcome measures will be the Limits of Stability (a force platform measure of balance) and the Step Test (a clinical measure of balance). Secondary outcomes include other balance and mobility measures, number of falls and falls risk measures, cognitive and behavioural measures, and carer burden and quality of life measures. Assessors will be blind to group allocation.

Longitudinal change in balance performance will be evaluated in a sub-study, in which the first 64 participants of the control group with mild to moderate severity Alzheimer's disease, and 64 age and gender matched healthy participants will be re-assessed on all measures at initial assessment, and then at 6, 12, 18 and 24 months.

**Discussion:**

By introducing a balance programme at an early stage of the dementia pathway, when participants are more likely capable of safe and active participation in balance training, there is potential that balance performance will be improved as dementia progresses, which may reduce the high falls risk at this later stage. If successful, this approach has the potential for widespread application through community based services for people with mild to moderate severity Alzheimer's disease.

**Trial registration:**

The protocol for this study is registered with the Australian New Zealand Clinical Trials Registry (ACTRN12608000040369).

## Background

Dementia is a major worldwide health problem among older people. It is one of the most burdensome conditions, and is a leading cause of disability and mortality in later life [1]. The prevalence of dementia is estimated to be 1.5% of people aged 65 years, and prevalence becomes more common with increasing age, reaching a level of 22% in people older than 85 years [2]. The global prevalence of dementia is forecast to double every 20 years, to 42.3 million in 2020 and to 81.1 million people in 2040 [3]. It is estimated that there will be more than one million people with dementia in the UK by 2025 [4]. The number of people with dementia is expected to triple in the United States by 2040 [5], and in Australia by 2050 [6]. Alzheimer's disease is the most common type of dementia, accounting for 50–70% of all dementias [7,8].

Falls are another major public health issue for the older population, with 30% percent of people aged 65 and over falling once or more each year [9,10]. Even higher falls rates have been reported for people with dementia, with around 42% of a community sample with mild-moderate dementia, and 60% of people with dementia in residential care falling at least once each year [11,12]. Decrease in balance performance is a strong indicator of falls in older people [13,14]. Greater balance and gait disturbances have been found in people with dementia when compared with older people in general [15,16], and these have been shown to occur in relatively early stages of the dementia pathway [17]. These declines in balance and motor performance may explain the increased incidence of falls in people with dementia, and have been shown to be a predictive factor for people with dementia needing permanent skilled nursing facility admission [18]. Increased carer strain has also been reported following a fall by care recipients [19].

There has been growing interest in the potential for improved outcomes associated with general exercise for people with cognitive impairment or dementia [20,21], and a number of different exercise approaches have been trialled. Exercise programmes targeting balance performance have been shown to improve balance and reduce falls in a range of community dwelling samples of older people [22-24], but none of these have included people with dementia [25]. While exercise programmes have been shown to be feasible for people with dementia [26,27], even at relatively advanced stages [28,29], these programmes usually primarily incorporate cardiovascular type exercises such as walking (or simple exercises for strengthening and flexibility). To reduce falls in older people, exercise programmes need to safely incorporate a challenge to the balance system [22-24], which requires substantially more complex movement combinations than cardiovascular or strength training exercise programmes. People with dementia are less likely to be able to successfully participate in these more complex movements at later stages of disease progression. Therefore, there is merit in exploring the feasibility and outcomes of balance training exercise programmes for people with mild to moderate severity dementia. Studies in older people living in the community who do not have dementia have demonstrated that improved balance performance from a balance exercise programme can be maintained for periods up to two years [30]. By introducing a balance training programme for people at mild to moderate levels of severity of dementia, it is anticipated that improved balance related outcomes may similarly persist well beyond the period of active engagement in the formal exercise programme. It is also possible that if this type of exercise programme becomes part of routines in earlier stages of the dementia pathway, that these exercises might be able to be continued as dementia progresses, rather than trying to introduce new tasks at later stages.

Given the high proportion of people with dementia who have a diagnosis of Alzheimer's disease, and varying symptoms and progression between people with different types of dementia [31], this study will focus recruitment on people with a diagnosis of Alzheimer's disease. To date, no study has evaluated a balance exercise programme designed to improve balance performance, specifically targeting community dwelling people with mild to moderate Alzheimer's disease.

The primary aim of the present project is to implement and evaluate the effectiveness of an individually tailored, home based exercise programme in improving balance and mobility performance in people with mild to moderate severity Alzheimer's disease. A sub-study will be run concurrently, with the aim of evaluating difference in rate of change in balance performance between people with Alzheimer's disease compared to healthy age and gender matched older people.

## Methods/design

### Study Design

The primary study is a single blind Randomised Controlled Trial (Figure 1). The CONSORT statement has been used as a framework for development of the methodology for this project. The sub-study is a longitudinal cohort study.

**Figure 1 F1:**
[figure not shown]
**Study design**.

### Participants Criteria

#### Participants with Alzheimer's disease

Participants will be included in the primary study if they have all of the following criteria: (i) a diagnosis of Alzheimer's disease; (ii) mild to moderate dementia (Clinical Dementia Rating Scale score of 0.5–2.0) [32]; (iii) independent mobility (walks outdoors with no more support than a single point stick); (iv) living in the community (ie not living in residential care); and (v) no other major neurological history (e.g. stroke with unilateral or bilateral paresis, multiple sclerosis) or orthopaedic history that impacts on functional mobility.

Participants will be excluded if they have a dementia diagnosis other than Alzheimer's disease; severe dementia (a Clinical Dementia Rating Scale of more than 2.0), limited mobility (doesn't walk away from home, or needs more support than a single point stick to walk outdoors); or presence of clinically significant aphasia (patient needs to be able to understand instructions in the exercise arm of the intervention).

Diagnosis of Alzheimer's disease will be confirmed through records from specialist Memory Clinics or by the treating general practitioner. Memory Clinics are multidisciplinary services established to provide early diagnosis and service provision information for patients with cognitive impairment and dementia and their families [33].

#### Healthy group (longitudinal sub-study)

Sixty-four healthy participants, age and gender matched to the first 64 people with Alzheimer's disease in the control group of the primary study, will be recruited from community advertisements such as newsletters and existing volunteer databases (ie the National Ageing Research Institute database). These participants will have no cognitive impairment (MMSE score ≥ 24) and no serious neurological or orthopaedic condition that impacts on balance and mobility performance, and will be community ambulant (regularly walks independently away from home).

### Measurements and Procedures

At baseline and at subsequent assessment occasions (Figure 1), the following measures will be used:

#### Measures of cognitive impairment and behavioural disturbances include

(i) Mini Mental State Examination (MMSE) [34], a widely used instrument for screening cognitive impairment. It comprises 11 items covering orientation, registration, attention and calculation, recall, language, a 3 step praxis item, and graphic copy of a geometric design.

(ii) Frontal Assessment Battery (FAB) [35], a short cognitive and behavioural battery to assess frontal lobe functions. The FAB consists of 6 subtests exploring conceptualization, mental flexibility, motor programming, sensitivity to interference, inhibitory control, and environmental autonomy. This test has been shown to distinguish frontotemporal dementia from Alzheimer's dementia [36].

(iii) Neuropsychiatric Inventory (NPI) [37], a screening questionnaire to assess 10 behavioural disturbances occurring in people with dementia, including delusions, hallucinations, agitation/aggression, dysphoria, anxiety, euphoria, apathy, disinhibition, irritability/lability, and aberrant motor activity. The NPI will be obtained from a caregiver familiar with the participant's behaviour.

#### Measures of balance and mobility performance

The following **laboratory measures **from the NeuroCom Balance Master™ long plate *(NeuroCom Balance Master™ Operator V3: CopyRight^©^2007) *will be used:

(i) Modified Clinical Test of Sensory Interaction of Balance (mCTSIB), the amount of postural sway is measured under four sensory conditions (eyes open and eyes closed, on a firm and a foam surface); (ii) Limits of Stability (LOS), a measure of the ability to weight shift forwards, backwards, to the right and the left in standing; (iii) stability during walking and turning; and (iv) stability during sit to stand. This test battery has been shown to have moderate to high test-retest reliability in assessing balance dysfunction in healthy older people [38] and clinical groups (eg stroke, Limits of Stability measures, ICC>0.84) [39] and to be sensitive to be able identify patients who have fallen and to be able to predict multiple falls [40].

A number of **clinical measures **of balance and mobility will also be used. These measures are simple and quick tests routinely used in clinical practice and research:

(i) Functional Reach (FR) test [41], a test of dynamic standing balance. The participant stands next to a wall with their feet 10 cm apart and dominant arm raised to 90 degrees. They are then asked to reach as far forward as possible without overbalancing and the distance of additional reach is recorded (cm).

(ii) Step Test [42], a test of dynamic standing balance. The number of times the participant steps one foot fully on and then off a 7.5 cm block step in 15 seconds is recorded. Each leg is tested separately, and worst side performance will be used for data analysis.

(iii) Timed Chair Stands [43]- global leg muscle strength will be measured by timing speed of standing up/sitting down five times from a 45 cm high chair, without using arms.

(iv) Timed Up and Go (TUG) test [44]-the participant is timed standing up from a standard chair, walking 3 metres with their usual speed, then returning to sit again in the chair (seconds). This task will be reassessed under dual task conditions, with a secondary cognitive task (counting backwards by 3's while performing the TUG), and with a secondary motor task (carrying a full cup of water while performing the TUG) [45].

#### Measures of falls and falls risk include

(i) the number of falls in the preceding 12 months will be collected from the participant or carer, based on retrospective recall; (ii) the Falls Risk for Older People (FROP-Com) [46], a detailed falls risk assessment tool evaluating 13 risk factors; and (iii) Physiological Profile Assessment (PPA) [47] abbreviated assessment, evaluating standing balance, hand reaction time, knee joint proprioception, visual contrast sensitivity and quadriceps muscle strength. The FROP-Com and the PPA have been shown to have good retest reliability (FROP-Com intra-rater and inter-tester reliability were 0.93 and 0.81 respectively, and the PPA retest reliability ranged from 0.50 to 0.97), and the FROP-Com to have moderate capacity to predict falls (sensitivity 71% and specificity 56%) [46,47].

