### Randomization

After baseline assessment, participants will be randomly allocated into the exercise or control groups. Randomization will be by computer generated random numbers table, with group allocation on a folded piece of paper in an opaque envelope, packed by a staff member independent of the project team. A research assistant independent of the assessors will identify group allocation, and communicate with the participant and their carer as to which group they are in, and make arrangements for the next stage of the project. In this way, assessors will be blind to the group allocation-randomization process at the time of the baseline assessment.

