### Intervention Group and Control Group Activities

**The control group **will continue with "usual care" for the subsequent six months without interruption, including all activities and service use recommended by treating health professionals. In addition, participants in the control group will receive a home programme involving six home visits for the six month period by an Occupational Therapist, to provide an information/education and support programme. Topics to be covered in the programme include issues around diagnosis; community services; occupational performance (including issues around grief and losses); and environmental safety and aids. The programme will avoid any messages encouraging any change in activities that may influence balance and mobility performance. Control participants will receive phone calls from the Occupational Therapist to follow up on issues raised in the home visits between home visits.

**The intervention group **will participate in a tailored (individualised) home based balance exercise programme, provided by a physiotherapist. This exercise programme is based on an existing home exercise programme (the Otago programme, ), which has been shown to improve balance and reduce falls in older people without cognitive impairment in the community setting [50-52]. The programme has been modified to provide increased support and visits in the early stages of exercising. Appropriate exercises from the Otago programme will be selected by the physiotherapist, and be tailored to balance and mobility problems identified from the assessments. Participants will receive six home visits during the six month duration (two visits in the first month after the baseline assessment, two further visits in the second month, then two more home visits four to six weeks apart for the remaining times). An exercise booklet will be provided by the physiotherapist to each participant or carer to give illustrations and instructions for the participant to continue the exercise programme at least five times a week. In between visits, the physiotherapist will contact participants by telephone (five phone calls during the six month duration). Adherence to the programme will be monitored by daily completion of an exercise diary. All participants will also continue to receive 'usual care'.

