### Follow Up Assessments

Six months after the initial assessment all participants will have all baseline measures repeated by an assessor blind to group allocation. Measures will be repeated six months later (ie 12 months after initial assessment) to determine sustained benefits from the programme.

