### Statistical Analysis

Intention to treat analysis will be used. Balance performance on the two primary outcome measures and the secondary outcome measures will be made using repeated measures ANOVA between the two groups, with variables differing between groups at baseline being used as covariates. Multivariate logistic regression will be used to evaluate factors associated with improved outcomes, including level of adherence to the exercise programme. For the longitudinal sub-study, independent sample *t*-tests will be used to determine differences in balance performance between both groups at each time point.

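### The 12-month falls look-back, repeated at the 6-month visit, takes in about six months before randomisation, and the overlapping windows do not separate the programme period from the follow-up period

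*Protocol article*

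**What the plan says.** The Abstract lists falls among the secondary outcomes: "Secondary outcomes include other balance and mobility measures, number of falls and falls risk measures". The section on falls and falls risk gives the only definition of that count: "the number of falls in the preceding 12 months will be collected from the participant or carer, based on retrospective recall".

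This definition sits under a lead-in that covers every visit: "At baseline and at subsequent assessment occasions (Figure 1), the following measures will be used". Follow Up Assessments repeats the instruction: "Six months after the initial assessment all participants will have all baseline measures repeated by an assessor blind to group allocation". It then gives the purpose of the later visit: "Measures will be repeated six months later (ie 12 months after initial assessment) to determine sustained benefits from the programme". Randomization fixes the order of events: "After baseline assessment, participants will be randomly allocated into the exercise or control groups".

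For the primary and secondary outcomes, Statistical Analysis plans "repeated measures ANOVA between the two groups, with variables differing between groups at baseline being used as covariates".

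No section gives a shorter recall period for the follow-up visits or describes a prospective record of falls.

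**The concern.** A visit 6 months after baseline that asks about the preceding 12 months collects about six months of falls that treatment could not have influenced. Those falls dilute any ratio comparison and add noise to any comparison of means. The 12-month visit then counts the programme-period falls a second time, together with those of the following six months.

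At stake is the reading of a named secondary outcome. An unremarkable falls result at 6 months could reflect the window rather than the exercise programme. A 12-month total could look favourable purely because of falls avoided during the programme, with nothing sustained afterwards. If only undated totals are collected, they cannot be split by period for each participant later.

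**Working it through.** **Inputs from the protocol article.** Recall window 12 months (falls and falls risk). Visits at 0, 6 and 12 months (Follow Up Assessments). Randomisation after baseline (Randomization). For illustration only: about 42% of a community sample with mild to moderate dementia falling each year (Background) and 80 evaluable participants per group (Sample Size). The article gives no power figure for falls, so there is none to reproduce.

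**Assumptions.** Constant underlying fall rate, accurate recall, and programme-period rate ratios R of 0.50, 0.65 and 0.80.

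**1. Windows.** Call the half-year counts *a* (months −12 to −6), *b* (−6 to 0), *c* (0 to 6, programme) and *d* (6 to 12, after the programme).

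| Visit | Window (months) | Records |
|---|---|---|
| Baseline | −12 to 0 | a + b |
| 6 months | −6 to +6 | b + c |
| 12 months | 0 to +12 | c + d |

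The share of the 6-month window before baseline is (12 − 6)/12 = 50%, and slightly more lies before randomisation, which follows the baseline visit. No visit records *c* or *d* alone. Subtracting the 6-month from the 12-month count gives *d − b*, not *d*.

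**2. Dilution of a rate ratio at 6 months.** Observed ratio = (6 + 6R)/12.

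- R = 0.50: 0.75
- R = 0.65: 0.825
- R = 0.80: 0.90

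On the log scale, ln 0.825 / ln 0.65 = 0.192/0.431 = 0.447, and ln 0.75 / ln 0.50 = 0.288/0.693 = 0.415.

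**3. Sample-size cost on the ratio scale (Poisson).** The longer window also holds more falls, so its variance is smaller. The variance of the log ratio is proportional to 1/6 + 1/(6R) for a 6-month window and to 1/12 + 1/(6 + 6R) for the 12-month window.

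- R = 0.65: 0.423 and 0.184. Multiplier (1/0.447²) × 0.184/0.423 = 5.0 × 0.436 = 2.2.
- R = 0.50: 0.500 and 0.194. Multiplier (1/0.415²) × 0.194/0.500 = 5.8 × 0.389 = 2.3.

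**4. Cost on the mean-count scale (Poisson).** With monthly rate λ, the expected difference is 6λ(1 − R) in either window, because *b* is balanced in expectation by randomisation. The variance of the difference rises from 6 + 6R to 12 + 6 + 6R, in units of λ.

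- R = 0.65: 21.9/9.9 = 2.2
- R = 0.50: 21/9 = 2.3

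**5. Overdispersion.** 42% a year corresponds to −ln(1 − 0.42) = 0.545 falls per year. With negative binomial dispersion k (assumed 0.5 to 2), 2k is added to the variance of the log ratio.

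- R = 0.65, k = 0.5: variances 10.32 and 5.06. Multiplier 5.0 × 0.490 = 2.5.
- R = 0.50, k = 2: variances 15.01 and 8.28. Multiplier 5.8 × 0.552 = 3.2.

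**6. Illustrative power**, comparing proportions of fallers at the 6-month visit (80 per group, two-sided 0.05, rate 0.545 per year). This is not the planned analysis; it only shows the scale of the loss.

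| R | Falls since baseline (6 months) | 12-month look-back |
|---|---|---|
| 0.50 | 23.8% v 12.7%, power 44% | 42.0% v 33.5%, power 20% |
| 0.65 | 23.8% v 16.2%, power 22% | 42.0% v 36.2%, power 11% |
| 0.80 | 23.8% v 19.6%, power 10% | 42.0% v 38.8%, power 6% |

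**The case against.** **The article condenses a longer protocol, and the follow-up form may ask something else.** This is possible, and it limits certainty about what will be asked. But the recall period and its repetition are stated, not left out. If the look-back was meant for baseline only, a named secondary outcome has no stated follow-up window. Either way the text needs correcting.

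**The planned analysis compares means, so nothing is biased.** This stands for mean counts: the loss there is precision. Neither scale carries a raised risk of a false positive. In expectation, the group contrast in *d − b* even estimates the months 6–12 difference. It does so only on the count scale, with the noise of *b* added, and only if the programme-period falls are recalled alike at both visits.

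**Falls are secondary.** This also stands. The aim is balance and mobility, the sample size was not based on falls, and the Discussion places the hoped-for reduction in fall risk at later stages of dementia.

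Three stronger readings are tempting but not supported:

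- *A five- to sixfold sample.* Squaring the shrinkage of the log ratio gives 5.0 to 5.8, but only with the variance held fixed. The 12-month window contains more falls, and step 3 brings the figure to 2.2 to 2.3.
- *An invalid 12-month falls comparison.* That window is essentially all after randomisation and supports a cumulative comparison.
- *Different ascertainment by arm because of the diary.* The article says: "Adherence to the programme will be monitored by daily completion of an exercise diary". That diary records exercise. Nothing says it records falls, both arms have six home visits and phone contact, and the follow-up assessor is blinded.

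**Conclusion.** The point holds for the 6-month falls count as the article words it. About half the window precedes randomisation. A rate ratio is pulled towards 1 (0.65 to 0.825, 0.50 to 0.75), while a difference in mean counts stays unbiased but less precise. The cost relative to a 6-month window is roughly 2.2 to 2.3 times the sample under Poisson counts, and about 2.5 to 3.2 times with the overdispersion assumed above. These sizes rest on a constant fall rate, accurate recall and assumed rate ratios, none of which the article supplies.

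The 12-month count is valid as a cumulative total but overlaps the 6-month count. By itself it cannot show the sustained benefit on falls that the visit is meant to assess.

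This is worth correcting before data collection because the change is so cheap. A reader might infer that it threatens the trial's main conclusion. It does not: the Limits of Stability and Step Test analyses are untouched.

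**What to change.** 1. Keep the 12-month look-back at baseline only, and use it as a covariate for the falls analysis. It should not be a level of the repeated factor, because its window differs in length from those at follow-up.
2. At the 6- and 12-month visits, record falls since the previous assessment and the date of that assessment. This gives non-overlapping 0–6 and 6–12 month counts: the first for the programme period, the second for sustainability.
3. State that the cumulative 0–12 month count is the sum of the two.

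The cost is one reworded question on the follow-up form. The statistical downside is fewer falls in each window, but the cumulative total is still available. The shorter interval also asks less of participants' and carers' memory.

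A prospective falls calendar used identically in both arms and checked at the phone calls already planned would be an optional improvement, at a small burden to participants and carers. The correction does not depend on it.
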